#### Intervention description {11a}

All participants will receive the electroacupuncture or sham electroacupuncture before the gastroscopy. They will then undergo standard upper gastrointestinal endoscopy procedures. Patients in both groups will be discharged within 1 h after the endoscopy, which includes a 30-min observation period, a preference for future endoscopy assessment and blinding assessment. The acupuncture methods are described in Table 1. To maintain blinding, patients will be asked to wear an eye-patch and receive treatment in a supine position in an isolated space with limited communication with the acupuncturist. The acupuncturist will disinfect the patient’s skin with 75% alcohol cotton balls before treatment. Acupuncture treatment will last 30 min. After removing the needle, researchers will use a clean cotton ball to compress the acupoint to prevent bleeding. A total of 8 points will be used. Table 2 summarizes the acupoints and rationale.

**Table 1 Tab1:** Treatment methods of electroacupuncture and acupoints

	EA group	SEA group
Acupoints	Hegu (LI4), Neiguan (PC6), Zusanli (ST36), Liangqiu (ST34)	Non-acupoints as shown in Table 3
Depth of insertion	10 mm:LI4 PC6;30 mm:ST36 ST34	Superficial acupuncture
Needle type	Steel needles (Wuxi Jiajian Medical Co. Ltd. Wuxi, China)	The same as EA group
Needle sensation	With de-qi sensation	Without de-qi sensation
Electric stimulation	Two pairs of needles:	Two pairs of needles:
	LI4–ST36 (bilaterally)	LI4–ST36 (bilaterally)
	Connected to CMNS6-1 (Wuxi Jiajian Medical Device CO., China)	Connected to CMNS6-1 (Wuxi Jiajian Medical Device CO., China)
	Deliver continuous wave-type low-frequency 2 Hz and current of 2 mA	No electrical current delivered

*EA* electroacupuncture, *SEA* sham electroacupuncture

**Table 2 Tab2:** Acupoint selection and rationale based on traditional Chinese medicine

Acupoint	Location	Traditional Chinese medicine indication	Suggested technique
LI4 (Hegu)	Dorsum of hand, at the level of the midpoint of the second metacarpal bone, between the first and second metacarpal bones	Relieve visceral pain	Needle perpendicular,0.5–1.0 cun
PC6 (Neiguan)	Palmar aspect of the forearm, between the tendons, 2 cun away from the transverse crease of the wrist	Reduce nausea and stomach pain	Needle perpendicular,0.5–1.5 cun

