After the gastroscopy procedure, researchers will evaluate the success of the blinding by asking participants the following question: “what kind of treatment do you think you have received?” The options are traditional acupuncture treatment, superficial acupuncture treatment, and uncertain. If participants do not choose “uncertain,” then the researcher will question the patient further for specific reasons.
Related to gastroscopy

The duration of the gastroscopy and the number of biopsies will be recorded after operation.

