**Others**								
Adverse events			X	X	X	X	X	X
Patient satisfaction							X	
Success of blinding							X	

*EA* electroacupuncture, *SEA* sham electroacupuncture, *VAS* visual analogue scales, *STAI-S6* six-item short form of the State-Trait Anxiety Inventory, *APAIS* Amsterdam Pre-operative Anxiety and Information Scale, *HR* heart rate, *BP* blood pressure, *SpO2* oxygen saturation

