## Assignment of interventions: blinding

### Who will be blinded {17a}

This is a patient-assessor-blinded study. To ensure that participants are blind, they will be treated in an isolated space and be required to wear blindfolds. Only the acupuncturist who performs the treatment will know the group assignment at the time of treatment. Gastroenterologists, data analysts, and statisticians will remain blinded.

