### Plans to promote participant retention and complete follow-up {18b}

Patients will come to the hospital 1 week after gastroscopy to complete the final questionnaires. We will follow up and debrief patients at this time point. At the end, patients will receive a transportation subsidy.

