### Data management {19}

Patient characteristics will be recorded in the CRFs and stored in the researcher’s office. The clinical trial management platform ResMan will be used to manage the raw data. The raw data will be collected by assessors who are blinded to the group assignment and repeated input methods will be used to ensure that the entered data is correct. Before the platform is officially launched, it will be tested and the users will be trained. After the platform is officially launched, the database will be locked with a password, which will only be known by relevant personnel. The clinical director will oversee the work of the clinical trial center at least once a month.

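### Questioning patients at the 30-minute visit about why they guessed an arm puts the blinding of the day-7 secondary outcomes at avoidable risk

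*Protocol article*

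**What the plan says.** The blinding check is described at the end of Secondary outcomes: "After the gastroscopy procedure, researchers will evaluate the success of the blinding by asking participants the following question". "The options are traditional acupuncture treatment, superficial acupuncture treatment, and uncertain". The next step is prescribed: "If participants do not choose “uncertain,” then the researcher will question the patient further for specific reasons".

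Table 4 has one mark for the row "Success of blinding", under 30 minutes after endoscopy, and none at day 7. Intervention description {11a} agrees. It has patients discharged within an hour of the endoscopy, a period "which includes a 30-min observation period, a preference for future endoscopy assessment and blinding assessment".

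On blinding, Who will be blinded {17a} says: "Only the acupuncturist who performs the treatment will know the group assignment at the time of treatment". Data management {19} says: "The raw data will be collected by assessors who are blinded to the group assignment".

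After one week patients return in person for the last questionnaires. For that visit, section {18b} adds: "We will follow up and debrief patients at this time point".

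**The concern.** A closed question on perceived allocation is a normal way to check masking. The weak point is the interview attached to it and its timing. A patient who picks an arm is asked by a member of staff to explain the choice, and a week later the same patient rates discomfort and states a preference again.

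Two routes to bias follow.

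- **Through the patient.** Someone who has committed to one arm and defended that choice may rate later symptoms in line with it. The preference item asks about interest in acupuncture before a next gastroscopy, so it is directly sensitive to what the patient believes they received.
- **Through staff.** The reasons will often concern what was felt during needling, and that is where the arms differ. A member of staff who hears them and later collects day-7 data may no longer be blinded in practice.

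At stake is the claim of patient and assessor blinding for the day-7 secondary outcomes. The Discussion relies on rigorous patient blinding, and on the acupuncturist staying out of questionnaire evaluation, to offset the one person who must know the allocation.

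**Working it through.** The plan gives no figure on this point to reproduce, so the check is mainly a comparison of its sections.

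**1. What comes before and after the interview**

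| Item | Source | Timing relative to the interview |
|---|---|---|
| Discomfort VAS, 30 min (primary) | Primary outcome; Table 4 | Same visit, order not stated |
| Preference, 30 min | Table 4; {11a} | Same visit; {11a} lists it before the blinding check |
| Discomfort VAS, day 7 | Secondary outcomes; Table 4 | Always after |
| Preference, day 7 | Table 4 | Always after |
| STAI-S6 and APAIS, day 7 | Secondary outcomes text only; Table 4 has no day-7 mark | After, if measured |
| Adverse events, day 7 | Table 4 | Always after; the text has patients and doctors record them |

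The order between the interview and day 7 is fixed by the schedule. It does not depend on any detail that a condensed article might omit. The disagreement over day-7 anxiety changes only how many later outcomes are affected.

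**2. Whether the reasons can reveal the arm**

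| Feature | EA | SEA |
|---|---|---|
| De-qi | Sought | Avoided |
| Depth | 10 mm or 30 mm, by point | 2–3 mm |
| Current | 2 Hz, 2 mA | None (device connected, set to zero) |

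Source: Table 1 and the two group descriptions. All three differences bear on what a patient may feel. A bare guess is not the allocation. A reason that refers to one of these sensations can point to the allocation; other reasons need not.

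**3. Who hears the reasons**

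Secondary outcomes names a researcher, and Data management names blinded assessors. The article does not say that they are different people, nor that the answers are kept from the assessors. Nor does it say that they are the same person. Exposure of the assessor is therefore possible but not established.

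**4. How many patients might be questioned**

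Input: 60 enrolled (Sample size {14}). Assumption: a share p does not answer uncertain. The documents give no value for p.

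Number questioned = 60 × p

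- p = 0.30: 60 × 0.30 = 18
- p = 0.50: 60 × 0.50 = 30
- p = 0.70: 60 × 0.70 = 42

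These count patients who would be interviewed. They do not count patients whose reasons reveal the arm, and they do not measure bias. Any loss before day 7 lowers the number who carry the exposure into the day-7 data.

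**The case against.** The case against has several sound parts.

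- **Primary outcome.** A reader might infer that the interview contaminates the 30-minute VAS, because both fall in the same visit with no stated order. The documents do not support this. Form order within a visit is a detail that an article may leave to the case report form, and {11a} lists the blinding check last, after observation and preference. The VAS would be exposed only if it were completed after the blinding question, and nothing says so.
- **Reasons are not the allocation.** Both arms are needled and connected to the same device, patients wear an eye-patch, and recent acupuncture users are excluded. Reasons may be vague, wrong or about symptom relief. It would go too far to say that the answers disclose the arm; some could.
- **Roles and wording.** The interviewer is not stated to be the outcome assessor. Section {17a} limits knowledge of assignment at the time of treatment, so an opinion heard later does not contradict it.
- **Self-report.** Patients complete the VAS and the day-7 questionnaires themselves, so an unblinded assessor has limited influence. This weakens the staff route but leaves the patient route, which matters at least as much.
- **No new cue.** Patients already know that there are two groups with equal chances (section {16b}). Knowing that is still different from choosing one and having to justify it.
- **Debrief.** A reader might infer that the day-7 debrief reveals allocation before the forms are completed. No section says that allocation is disclosed, and the unblinding section sees no need for it.
- **Early timing.** Asking for the guess soon after treatment is defensible. That supports an early closed guess, not an early interview about reasons.

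**Conclusion.** The point holds for the day-7 secondary outcomes. The protocol prescribes oral questioning about reasons for every patient who names an arm, and its own schedule puts this before the day-7 VAS and preference items (and before STAI-S6 and APAIS, if the outcomes text governs). This creates an avoidable risk of priming the patient. Possible unblinding of staff is a further risk, conditional on who conducts the interview and on what patients say.

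The primary outcome is not shown to be affected. The documents allow no estimate of bias. The range of 18 to 42 of 60 rests on assumed shares of 30% to 70% and describes only how many patients might be interviewed. The point deserves a change to the plan because the procedure is explicit and the alternative is cheap. It does not undermine the main comparison.

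**What to change.** Keep the closed three-option guess at the 30-minute visit, and state that it is the last form, after the VAS and preference items. Do not probe reasons orally at that visit. Then choose one of two ways to obtain them:

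1. The patient writes the reason and seals it, and it is opened only after database lock.
2. The reasons are asked for at the day-7 visit, once all day-7 questionnaires are complete.

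The cost is a sentence in the blinding section, the page order of the case report form and, for the first option, one envelope per patient. The downside is small: written reasons may be less detailed than an interview, and reasons given at day 7 are recalled a week later.

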### Participant timeline {13}

The timing of intervention and data collection is detailed in Table 4.

**Table 4 Tab4:** Schedule of enrolment, intervention, and assessments

Timepoint	Screening	Baseline	Intervention		Operation			Follow-up
			Before	After	Before	During	30 min after endoscopy	Day 7
**Basic information**								
Informed consent	X							
Inclusion/exclusion	X	X						
**Interventions**								
EA			X	X				
SEA			X	X				
**Assessments**								
**Primary outcome**								
Discomfort VAS							X	
**Secondary outcomes**								
Discomfort VAS							X	X
STAI-S6			X	X				
APAIS			X	X				
HR BP and SpO2					X	X	X	
Preference in a future endoscopy							X	X
The duration of the gastroscopy							X	
The number of biopsies							X	
**Others**								
Adverse events			X	X	X	X	X	X
Patient satisfaction							X	
Success of blinding							X	

*EA* electroacupuncture, *SEA* sham electroacupuncture, *VAS* visual analogue scales, *STAI-S6* six-item short form of the State-Trait Anxiety Inventory, *APAIS* Amsterdam Pre-operative Anxiety and Information Scale, *HR* heart rate, *BP* blood pressure, *SpO2* oxygen saturation

### Sample size {14}

Hypotheses: We hope to provide conclusive evidence to test the hypothesis that acupuncture is superior than sham acupuncture in reducing the discomfort of patients during gastroscopy. In our pilot study, the discomfort VAS assessment at 30 min post-procedure was 4.8 (SD, 1.76) in the EA group and 6.3 (SD, 1.53) in the SEA group. We used PASS software to calculate that 50 patients would be needed to provide a 90% power to detect a difference of discomfort VAS in 2 groups at a 2-sided significance level of 5%. If we assume that 20% of patients would be lost to follow-up, 60 would need to be enrolled.

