## Assignment of interventions: allocation

### Sequence generation {16a}

In this trial, we plan to use SPSS24.0 software to generate a random number table, which divides eligible participants into the EA group or SEA group with a 1:1 ratio.

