### Methods in analysis to handle protocol non-adherence and any statistical methods in analysis to handle protocol non-adherence and any statistical methods to handle missing data {20c}

We perform statistical analysis on complete case.

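### The enrolment of 60 is 50 × 1.2 rather than 50 / 0.8, so at the protocol's own 20% loss 48 patients are analysed, not 50; a small error, worth about 1.3 points of power

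*Protocol article*

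**What the plan says.** The Sample size section {14} of the protocol article gives its inputs and both results. In the pilot, "the discomfort VAS assessment at 30 min post-procedure was 4.8 (SD, 1.76) in the EA group and 6.3 (SD, 1.53) in the SEA group". From these, PASS is reported to show that "50 patients would be needed to provide a 90% power" at a two-sided 5% level. The allowance for loss follows: "If we assume that 20% of patients would be lost to follow-up, 60 would need to be enrolled".

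Sequence generation {16a} fixes equal allocation. Statistical methods {20a} leaves patients who drop out out of the analysis, and names the t-test and the rank-sum test for continuous measures. The missing-data section {20c} says "We perform statistical analysis on complete case". The article describes no replacement of patients who drop out.

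**The concern.** The number enrolled, less the expected loss, should give back the number required. Here it does not: 60 less 20% is 48, while the requirement in the preceding sentence is 50. Because lost patients are neither replaced nor imputed, nothing later in the plan makes up the difference.

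What is at stake is whether the stated power is accurate. The 90% figure would be carried into the trial report and would colour how a null result is read. The Discussion also expects this trial's data to inform the sample size of larger trials, so the calculation may be copied.

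**Working it through.** **Inputs** (Sample size {14} unless noted)
- Means 4.8 (EA) and 6.3 (SEA): difference 6.3 − 4.8 = 1.5
- SDs 1.76 and 1.53
- Two-sided alpha 0.05, power 0.90
- Required 50, loss 20%, enrolled 60
- Allocation 1:1 (Sequence generation {16a}); complete cases ({20a}, {20c})

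**Step 1: reproduce the 50.**
Common SD = √((1.76² + 1.53²)/2) = √(5.4385/2) = 1.649. Standardised difference = 1.5/1.649 = 0.910.
Normal approximation, with (1.960 + 1.282)² = 10.507:
n per arm = 10.507 × 5.4385 / 1.5² = 25.4, so 26 per arm, 52 in total.
This is within two patients of the stated 50, so the protocol's figure is reproduced to a reasonable tolerance.

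**Step 2: reproduce the 60.**
50 × 1.2 = 60 exactly. The formula for a 20% loss is N/(1 − 0.20):
50 / 0.8 = 62.5, so 63, or 64 for equal arms.
Check: 64 × 0.8 = 51.2, which meets 50; 60 × 0.8 = 48, which does not.
Largest loss at which 60 still leaves 50: 1 − 50/60 = 16.7%.

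**Step 3: power at the numbers analysed.**
Noncentral t with noncentrality 1.5 / (1.649 × √(1/n₁ + 1/n₂)) and n₁ + n₂ − 2 degrees of freedom, beside the normal approximation:

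| Analysed | Exact t | Normal |
|---|---|---|
| 48 (24 + 24) | 87.0% | 88.3% |
| 50 (25 + 25) | 88.3% | 89.6% |
| 52 (26 + 26) | 89.5% | 90.7% |
| 53 (27 + 26) | 90.1% | – |
| 54 (27 + 27) | 90.7% | 91.7% |
| 60 (30 + 30) | 93.4% | 94.1% |

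Allowing the two SDs to differ (Welch) changes the equal-arm figures by less than 0.1 point.

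**Step 4: divide the shortfall.**
Total gap by exact t: 90 − 87.0 = 3.0 points.
- Inflation step, 50 down to 48: 88.3 − 87.0 = about 1.3 points
- The 50 itself: 90 − 88.3 = about 1.7 points

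If the 50 is taken to give exactly 90%, 48 gives about 88.8%, again a loss of a little over one point.

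**Step 5: how firm is the 1.7-point part?**
The pilot means are printed to one decimal, so the unrounded difference could lie between about 1.4 and 1.6. With the SD held at 1.649, exact-t power is:

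| Difference | 25 per arm | 24 per arm |
|---|---|---|
| 1.45 | 86.1% | 84.7% |
| 1.50 | 88.3% | 87.0% |
| 1.55 | 90.3% | 89.0% |

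Rounding alone can therefore remove or enlarge this part. It does not affect step 2, which uses only 50, 20% and 60.

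**Step 6: the loss that 60 can bear.**
By exact t on the printed figures, 53 analysed (27 + 26) is the smallest total reaching 90%. That allows 60 − 53 = 7 missing patients, 7/60 = 11.7%, if spread evenly over the arms.

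**The case against.** The strongest objection is that the 20% hardly applies to the primary outcome. The Outcomes section takes the primary VAS at 30 minutes, and the Intervention description places a 30-minute observation period before discharge within an hour. Loss to follow-up more naturally means failure to return at day 7, which carries only secondary outcomes and safety. If complete-case analysis is applied outcome by outcome, a day-7 absence leaves the primary comparison intact, and power with all 60 is 93.4%. This stands as a reason to expect the actual shortfall to be smaller, or absent. It does not repair the text: the protocol applies its 20% to the primary-outcome calculation, and {20a} can be read as removing a patient who drops out from every analysis.

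The second objection is size: two patients and about 1.3 points. That stands, and sets the weight of the point.

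The third concerns the 50. A reader might infer that it is simply wrong, or that the whole gap from 90% to 87% comes from the loss formula. The documents support neither. More than half of the gap lies in the 50, and whether the 50 is short depends on rounding of the pilot means and on PASS settings that the article does not give. Software settings cannot explain the 60, since no setting turns 60 with 20% lost into 50 analysed.

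**Conclusion.** The inflation step is wrong on the protocol's own figures: 60 enrolled with 20% lost leaves 48, not 50, and the matching enrolment is 63, or 64 for equal arms. This conclusion needs no outside assumption.

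On the printed pilot values, with complete cases and 24 per arm, the stated 90% power is not delivered. It is about 87% by exact t and 88% by the normal approximation, with about 1.3 points due to the inflation step. The power figures assume a difference of exactly 1.5, a common SD of 1.649, roughly normal scores and even loss between arms. The further statement that 53–54 rather than 50 would be needed holds only on the rounded values.

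A reader might go on to infer that the trial is materially underpowered or must enrol more patients. That does not follow: the shortfall is small, and the primary VAS is collected before discharge. This is a minor arithmetic correction.

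**What to change.** Keep 60 and reword the end of the Sample size section, for example: *Sixty enrolled patients give about 87–88% power if 20% have no 30-minute VAS, and about 90% power if no more than about 7 patients (roughly 11%), spread evenly across the arms, have none.* State that the loss relevant to this calculation is a missing 30-minute VAS, and that absence at day 7 does not remove a patient from the primary analysis.

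If the claim of 90% power at 20% loss is to be kept instead, change the enrolment to 63, or 64 for equal arms, which restores the protocol's own 50. Giving the PASS procedure and the unrounded pilot means would settle whether 50 is sufficient.

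The first option costs one reworded paragraph and a slightly lower stated power, with no added patients. The second costs three or four more patients.

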### Recruitment {15}

Participants of the study will be recruited through the outpatient clinic or inpatient, hospital-based WeChat advertising, and posters in the Shanghai Municipal Hospital. Any patients who are willing to participate will be screened by telephone or on site and consented for the study. There is one specialist who will answer the phone to answer questions from these kinds of disposed patients.

Research assistants will screen the patients, obtain written informed consent, and assign them to either the EA or SEA group, to receive a traditional acupuncture or an acupuncture-like simulation treatment.

## Assignment of interventions: allocation

### Sequence generation {16a}

In this trial, we plan to use SPSS24.0 software to generate a random number table, which divides eligible participants into the EA group or SEA group with a 1:1 ratio.

### Concealment mechanism {16b}

A random distribution card will be made and sealed with an opaque envelope. Participants will be informed that they have an equal chance of being assigned to the EA or SEA group before the trial.

### Implementation {16c}

An independent researcher, blinded to the study protocol, will generate the allocation sequence. Another researcher will give the opaque envelope to the acupuncturist according to the timing sequence of participant registration for the trial. Then, the acupuncturist will open the envelope to perform the corresponding acupuncture operation.

